## Abstract

**Background:**

An unacceptably high percentage of our nation’s low-income, minority youth (age<18 years) are not regularly physically active. One reason for this could be their lack of access to quality youth physical activity opportunities (YPAOs). Our previous research found that small businesses (<500 employees), which represent over 99.64% (27.9/28.0 million businesses in United States) of all employers, are powerful resources for creating and improving YPAOs. In accordance with the socioecological model and established philanthropic principles, we developed an alpha version of an intervention (alpha-i) for increasing small businesses’ involvement with YPAOs.

**Objective:**

The aims of this proposed study are to (1) create a beta version (beta-i) of the intervention and (2) conduct a pilot study of its impact on small business support for YPAOs and YPAO utilization by the youth in low-income, minority neighborhoods.

**Methods:**

The alpha-i will be refined using information from focus groups and surveys conducted with small business owners and managers, YPAO providers, and parents and guardians of the youths from low-income, predominantly minority neighborhoods. A cluster randomized controlled trial will then be conducted for 1 year to examine the effects of the refined intervention (beta-i) on small business support for YPAOs in 10 low-income, minority neighborhoods. The control group of neighborhoods (n=10) will be provided with a standard practice intervention. The primary outcome for aim 2 will be the percentage of small businesses not supporting YPAOs at baseline that subsequently provide support for YPAOs at follow-up. We also will consider the US dollar equivalent of all types of support (monetary, goods/services, and time) donated for YPAOs by small businesses. In addition, we will examine the impact of the increased small business support for YPAOs on YPAO utilization by the youth.

**Results:**

As of May 1, 2019, all YPAOs and small businesses in the study neighborhoods have been identified, and surveys have begun with these groups. In addition, 9 focus groups were completed, and the data have been transcribed. We anticipate that manuscripts regarding these aspects of the study will be submitted in fall 2019.

**Conclusions:**

The proposed study is significant because it will provide evidence that an easily replicated approach can be used to increase small business support for YPAOs and that this support results in greater use of the YPAOs by youth. A logical next step will be to determine if YPAO changes resulting from increased small business support positively influence youth physical activity levels.

**ClinicalTrial:**

ClinicalTrials.gov NCT03936582; https://clinicaltrials.gov/ct2/show/NCT03936582.

**International Registered Report Identifier (IRRID):**

DERR1-10.2196/13141

## Introduction

### Background

Health benefits can be gained by the youths (age<18 years) who regularly participate in physical activity; for example, physical activity reduces the incidence of overweight, obesity, and chronic diseases [1-4]. Unfortunately, many youths fail to engage in adequate levels of physical activity. National data show that 3 out of 4 youths (aged 12-15 years) do not meet physical activity guidelines for moderate to vigorous physical activity (MVPA), and 7.6% are not involved in MVPA at all [5]. The problem is even more glaring for the minority youth. The 2013 Youth Risk Behavior Surveillance survey indicated that 21.5% of minority youth, compared with 12.5% of nonminority youth, were performing less than the recommended 60 min per week of MVPA [6]. In 1995, similar findings were reported—the minority youth participated in less MVPA than their nonminority peers [7]. This persistent difference has undoubtedly contributed to the disproportionately high burden of disease currently seen in the low-income, minority youth. Recent estimates indicate that 8.0% of African American children (aged 2-19 years) are considered severely obese versus only 3.9% of white children and the incidence of type 2 diabetes is a staggering 5 times higher [8-10]. Given their typically poor outcomes, it is unlikely that school-based physical education (PE) or physical activity interventions conducted in isolation (ie, individual level) will have a sufficient positive impact on physical activity [6,11]. Although over half of the high school youth are enrolled in PE, only 29% attend class on a daily basis and less than half are actually physically active during class [12]. Clearly, discovering innovative ways to enable and encourage the low-income, minority youth to be more physically active is a public health priority, requiring novel ideas and sustainable solutions.

The socioecological model has been used to explain why the youth are not more physically active. Briefly, the model suggests physical activity behavior is determined by intrapersonal (eg, self-motivation), interpersonal (eg, social support), and environmental (eg, availability of programs) factors [13]. Although intrapersonal and interpersonal factors have been studied extensively, they have not been shown to adequately explain youth physical activity or provide a basis for the development of effective interventions for the youth [14]. On the other hand, the evidence supporting a role of the environmental factors has grown exponentially in recent years [15-18]. Community sprawl, safety concerns, pedestrian-unfriendly street designs, and increases in sedentary activities (eg, television), among others, have a negative effect on youth physical activity and fitness [19-23].

Perhaps the strongest and the most influential environmental determinants of youth physical activity are the availability and adequacy of youth physical activity opportunities (YPAOs). They have been defined as programs and places available to the youth with components/amenities that typically require/involve physical activity [24-28]. A park with sports fields or playgrounds or a dance class at a community center are good examples. Significant associations have been found between youth physical activity and access to affordable YPAOs, and lack of YPAOs has been cited by the youth as a major barrier to being active [24,29-35]. The quality of the YPAOs (eg, staff training and equipment) also plays a role and has been shown to be as vital for increasing youth physical activity as having access to YPAOs [21,36,37-40]. Health-related fitness, including body fatness, has been associated with YPAOs, and the youth involved with YPAOs learn sportsmanship, acquire new skills, improve social skills, and are more likely to participate in physical activity as adults [15,41-45].

YPAOs assume added importance if they are in one’s local environment or neighborhood. Walking by the youth (aged 5-20 years) is positively associated with having access to nearby (<1 km distance from home) recreation or open spaces [46]. Middle school children engage in more physical activity if they have available after-school programs and high-quality local facilities near home [25]. Children provided with a safe schoolyard in their neighborhood become more physically active than children not granted such an amenity [21]. Others have shown that recreational facilities closer to home are more likely to be used than facilities located elsewhere and that local neighborhood characteristics, especially the presence of trails and places for physical activity, play a role in leisure activity patterns [24,26,47]. The presence of YPAOs varies between neighborhoods, with economically disadvantaged and minority neighborhoods having significantly fewer YPAOs than more affluent neighborhoods [48-52]. This deficiency, along with concerns about transportation and YPAO expenses, is expressed significantly more often by the parents of the minority youth than the parents of the nonminority youth [31]. Few YPAOs and associated expenses have been cited as critical barriers to reversing physical inactivity among the low-income, minority youth [53-56].

Small businesses (<500 employees) represent 99.64% (27.9/28.0 million) of all businesses operating in the United States. Total revenues typically exceed US $1 trillion annually and over half a million new businesses start each month [57]. More than one-fifth of small businesses are minority-owned with revenues totaling nearly US $700 billion [58]. Established philanthropic principles have been used to explain behaviors of different types of entities including small businesses [59-66]. Event sponsorship or sponsorship marketing refers to supporting various types of initiatives ranging from educational partnerships to YPAOs [59]. Small businesses heavily engage in event sponsorship compared with large businesses and they prefer to contribute to events connected to their local neighborhood [60-62,64]. It allows them to reach their target market more efficiently, expose their product/service directly to the market, give back to the neighborhood that supports them, and present an image of a socially responsible organization [63]. These actions can lead to increased consumer support and ultimately greater revenue [65,66]. Not surprisingly, when small businesses decide to support an initiative, they tend to sustain that support [67].

The strong preference by small businesses for sponsoring local programs sets up a powerful force that, if utilized effectively, would have a dramatic and lasting impact on the quantity and quality of YPAOs and, ultimately, physical activity and health in low-income, minority neighborhoods. Supporting this contention are findings from our preliminary study showing that although a majority of small businesses do not currently support YPAOs (~60%), a large percentage (88%) of these non-YPAO supporters believe they should [67,68].

### Objectives

In accordance with the socioecological model and established philanthropic principles, we developed an alpha version of an intervention (alpha-i) for increasing small businesses’ involvement with YPAOs. We are now poised to create a beta version (beta-i) and conduct a pilot study of its *impact* on small business support for YPAOs and *YPAO utilization by the youth* in low-income, minority neighborhoods. To meet this objective, we will complete the following specific aims and address the specified hypotheses.

*Aim 1:* Refine alpha-i components by conducting focus groups with small business owners, YPAO providers, and parents and guardians of the youth from low-income, predominantly minority neighborhoods. Results of the qualitative analysis will inform final tailoring of the intervention to create the beta-i that will be tested in aim 2.

*Aim 2:* Determine the effect of the beta-i on small business support for YPAOs by conducting a cluster randomized controlled trial with randomization at the neighborhood level. The intervention neighborhoods (n=10) will receive the beta-i, whereas the control neighborhoods (n=10) will be provided a standard practice intervention for a period of 1 year.

*Hypothesis 1:* The beta-i will result in a significantly greater increase in the percentage of small businesses providing support (eg, monetary donations) for YPAOs than a standard practice intervention.

*Hypothesis 2:* The US dollar equivalent of all types of support (monetary, goods/services, and time) donated for YPAOs by small businesses exposed to beta-i will be greater than that donated by small businesses exposed to the standard practice intervention.

*Aim 3:* Examine the impact of the increased small business support for YPAOs on YPAO utilization by the youth. The primary outcome will be the percent change in the number of youths participating in YPAOs from baseline to follow-up.

*Hypothesis 3:* The percent increase in youth participants from baseline to follow-up will be significantly greater at YPAOs in the treatment neighborhoods receiving support from small businesses than at YPAOs in the control neighborhoods.

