#### Study Neighborhood Identification

We used a multistep process recommended for use in urban health research to identify 27 distinct neighborhoods in New Castle, Delaware (mainly Wilmington, the largest city in the state) meeting our inclusion criteria requiring a minority concentration greater than 50%, median household yearly income in the lower third of all neighborhoods in these areas, and a land use mix that is at least 30% residential and at least 15% retail/commercial [77]. From the pool of 27 neighborhoods meeting our inclusion criteria, 20 were randomly selected to participate in the pilot study of the beta-i. Pairs of neighborhoods separated by at least 0.5 miles constituted the randomization unit with 1 randomly assigned to the treatment and the other to the control (see *Interventions* section later in this paper for a description of the study arms). This helped reduce the risk of contamination.

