The final activities that were completed in aim 1 involved the refinement of alpha-i components by the local advisory board, mainly using focus group and survey outcomes, and the formation of the beta-i. We also prepared for baseline data acquisition and developed the tracking mechanism that will be used to monitor donations to the fund and the distribution of donations. This will allow us to closely examine the cost of fund administration. We will be interested in the costs to solicit, maintain, and track donations, offer recognition (process and materials), identify YPAO providers, and distribute funds to YPAO providers. Information from donors and YPAO providers will include name, location, contact information, and a detailed description of the donation (given or received). Because donations could be monetary (US dollars) and nonmonetary (goods/services and time), we will use the Statement of Financial Accounting Standards 157, Fair Value Measurements guide, to properly determine the US dollar value of all donation types. By the end of May 2019, the development of the beta-i was complete.

### Procedures for Aim 2

The timeline of activities involved in aim 2 is presented in Multimedia Appendix 3. During May and June, we completed baseline assessments on small businesses and YPAOs. The beta-i and the control intervention will then be implemented from July 2019 to June 2020. Follow-up assessments, which will mirror baseline assessments, will be conducted from July to August 2020. The project completion date is set for the end of August 2020.

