#### Interventions

As stated previously, the treatment intervention (beta-i) will be a derivative of the alpha-i intervention components given in Multimedia Appendix 2. The control intervention is based on the finding that under normal circumstances, small business owners are seldom asked to provide support for specific initiatives in their neighborhood and they almost never receive educational material about the benefits of supporting neighborhood initiatives. Usually they are just made aware of organizations (eg, nonprofits) accepting donations [67]. In keeping with this *standard of practice*, small businesses in the control neighborhoods will be offered a minimal intervention with an opportunity to donate to a fund supporting YPAOs. This fund will be established at our institution for credibility and tracking purposes. However, donors to the control fund will not be able to select specific YPAOs to support, donate directly to their neighborhood, or receive recognition for their donations. In addition, the email messages they receive will not utilize a marketing strategy and only contain basic information for donating along with contact information if they have any questions. A local advisory board will not be formed, and liaisons will not be used in the control neighborhoods. Email distributions in the control neighborhoods will coincide with those made in the treatment neighborhoods. Donations to the control fund will be given to groups not operating in the study neighborhoods to further their mission to provide the youth with low-cost obesity treatment options, such as YPAOs. Provided in Multimedia Appendix 4 is a description of the interventions.

### Procedures for Aim 3

Data for aim 3 will be collected at baseline and follow-up as per the measures described under aim 2 as well as additional measures described below and used to address our aim 3 hypothesis. These additional measures will be conducted at baseline and follow-up.

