The primary outcome for aim 3 will be the percent increase in youth participants from baseline to follow-up. We hypothesize that the increase will be significantly greater at YPAOs in the treatment neighborhoods receiving support from small businesses than at YPAOs in the control neighborhoods. Previously in low-income, minority neighborhoods, we found an average of 46.7 (SD 37) youths participating in YPAOs [52,90]. With the proposed sample size of 10 neighborhoods per condition from aim 2, our pilot parameter estimates, an ICC of 0.05, and a desired power of at least 80%, we would need 35 YPAO assessments per condition to detect a difference of 0.5 percentage points between conditions at posttest. We expect a total of 140 YPAOs in our 20 study neighborhoods with 20% (28/140) being eligible for SOPARC assessments [52]. Given a 15% to 17% attrition rate and a response rate of 60%, we will randomly select 90 YPAOs for interviews to yield 44 YPAOs with baseline and follow-up data from the survey. These will be combined with the 28 YPAOs observed, giving a total of 70.

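### Hypothesis 3, as worded, compares only business-supported YPAOs in the treatment arm with all control YPAOs; this is not a comparison of the randomized groups and does not fit the per-condition sample size.

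*Protocol article*

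**What the plan says.** In Objectives, aim 3 is to "Examine the impact of the increased small business support for YPAOs on YPAO utilization by the youth". Hypothesis 3 then predicts that the percent increase in participants will be "significantly greater at YPAOs in the treatment neighborhoods receiving support from small businesses than at YPAOs in the control neighborhoods". Sample Size Determination for Aim 3 names the outcome ("The primary outcome for aim 3 will be the percent increase in youth participants from baseline to follow-up") and repeats the prediction in nearly the same words: "the increase will be significantly greater at YPAOs in the treatment neighborhoods receiving support from small businesses than at YPAOs in the control neighborhoods". In both places the support condition is attached to the treatment side only.

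Three other sections bear on this:

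- **Study Neighborhood Identification.** Neighborhoods were paired, and each pair "constituted the randomization unit with 1 randomly assigned to the treatment and the other to the control". YPAOs were not randomized to support.
- **Procedures for Aim 2.** "The beta-i and the control intervention will then be implemented from July 2019 to June 2020". Support prompted by beta-i therefore comes after randomization and baseline. Measuring Youth Physical Activity Opportunity Utilization describes donated funds as something providers may receive, not something they will receive.
- **Interventions.** In the control arm, "donors to the control fund will not be able to select specific YPAOs to support, donate directly to their neighborhood", and the money goes to groups outside the study neighborhoods.

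The same sample size section requires 35 YPAO assessments per condition and plans a total of 70 over the two conditions.

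**The concern.** Random assignment of neighborhoods makes the full sets of treatment and control YPAOs comparable. It does not make the supported treatment YPAOs comparable with all control YPAOs. If support tends to go to YPAOs that would have grown anyway, a difference appears without any effect of beta-i or of support. If it tends to go to struggling ones, a real benefit is masked. No matching control subset can arise through the study fund, because control donations leave the study neighborhoods. Control YPAOs supported in other ways stay mixed with unsupported ones. Unsupported treatment YPAOs drop out of the contrast, so any youths who moved from them to supported ones would count as gain with no offsetting loss.

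The Abstract's conclusion says the study will show that support leads to greater use by youth. A contrast selected in one arm cannot carry that causal statement.

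**Working it through.** **1. The plan's own figure.** Stated inputs: 10 neighborhoods per condition, ICC 0.05, power at least 80%, mean 46.7 (SD 37) youths, 35 YPAOs per condition, difference 0.5 percentage points. Alpha is not stated for aim 3; 0.05 is assumed. With 35/10 = 3.5 YPAOs per neighborhood, the design effect is 1 + (3.5 − 1) × 0.05 = 1.125. Then n per arm = 1.125 × 2 × [37 × (z_alpha + 0.842)/difference]².

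- 0.5 percentage points of the mean (0.2335 youths): about 443,000 two-sided.
- 0.5 SD (18.5 youths): 71 two-sided, 56 one-sided.
- 50% of the mean (23.35 youths): 45 two-sided, 34.9 one-sided.

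So 35 is recovered only as a 50% difference tested one-sided, and neither is stated. That is a separate matter. What counts here is that 35 is the number for a whole condition.

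**2. What the restricted contrast does to the sample.** Let s be the share of treatment YPAOs supported (not in the documents). The treatment group falls from 35 to 35s. Its design effect is 1 + max(3.5s − 1, 0) × 0.05, and SE = sqrt(design effect/(35s) + 1.125/35) in SD units. On the reading that recovers 35 (difference 23.35/37 = 0.631 SD, one-sided), power is:

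| s | Treatment YPAOs | Power |
|---|---|---|
| 100% | 35 | 80% |
| 75% | 26.25 | 75% |
| 50% | 17.5 | 67% |
| 25% | 8.75 | 50% |

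The stated power therefore belongs to a comparison by arm, not to the hypothesis as worded.

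**3. Bias and false-positive rate with no true effect.** Let r be the correlation between being supported and the YPAO's own change (also not in the documents). With normal-threshold selection, bias = r × φ(z_s)/s, where z_s cuts off the upper share s. The factor φ(z_s)/s is 1.271, 1.097, 0.798 and 0.424 at s = 25%, 33%, 50% and 75%. The two-sided rejection rate at nominal 5% follows from bias/SE. Example, s = 50%, r = 0.3: bias = 0.3 × 0.798 = 0.24 SD; SE = sqrt(1.0375/17.5 + 1.125/35) = 0.302; rejection 12.4%.

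| s | r = 0 | r = 0.2 | r = 0.3 | r = 0.5 |
|---|---|---|---|---|
| 25% | 5% | 0.25 SD, 10.2% | 0.38 SD, 16.9% | 0.64 SD, 38.3% |
| 33% | 5% | 0.22 SD, 9.7% | 0.33 SD, 15.9% | 0.55 SD, 35.5% |
| 50% | 5% | 0.16 SD, 8.2% | 0.24 SD, 12.4% | 0.40 SD, 26.1% |
| 75% | 5% | 0.08 SD, 6.1% | 0.13 SD, 7.6% | 0.21 SD, 12.3% |

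**4. Check by simulation** (3,000 trials per setting, Welch t test on neighborhood means). Rejection was 4.3-4.8% at r = 0 for the three supported shares simulated (25%, 50%, 75%), 6.2% at s = 75% and r = 0.2, 10.4% at 50% and 0.3, and 32.5% at 25% and 0.5. With all treatment YPAOs kept, it was 4.2-4.9% whatever the value of r.

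**5. Negative r.** The biases change sign. At s = 50% and r = −0.3, a true 0.631 SD benefit would appear as 0.631 − 0.239 = 0.392 SD. One-sided power is then Φ(0.392/0.302 − 1.645), about 36%, against 67% at r = 0.

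**The case against.** A reader might infer that the investigators have settled on discarding unsupported treatment YPAOs, and that the result will favor beta-i because donors will pick the growing ones. The documents support neither.

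On the first, the words about receiving support can grammatically attach to the neighborhoods, which would make the contrast all treatment v all control YPAOs. The sizing by whole condition fits that reading, as does the intention in Approach to Analysis to compare YPAO utilization graphically between the two study conditions. That section states no model for youth participation, and the analysis set may be defined in a document not shown. This stands, and it makes the defect one of wording and internal conflict. It does not remove it: aim 3 is about support for YPAOs, so the supported-YPAO reading is the natural one, and it appears twice, once beside the primary outcome.

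On the second, donor choice in the treatment arm is inferred from what control donors cannot do; the treatment description is in appendices not shown. No section says which YPAOs would attract support. Visibility or good management concerns the level of use, while bias here needs a link with change. The displacement of youths is likewise only a possibility. This also stands, so no single error rate can be put forward as the expected one.

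Finally, aim 3 asks about support rather than assignment, in a pilot. That is a legitimate question, but the comparison that answers it is observational, and the article presents it as a significance test leading to a causal conclusion.

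**Conclusion.** The concern holds as a defect of the stated hypothesis. Read naturally, Hypothesis 3 conditions on a post-randomization event in one arm, and it is inconsistent with a sample size that counts every assessed YPAO in each condition. The size and direction of bias cannot be known from the documents. Over the assumed range shown, the two-sided error runs from the nominal 5% (support unrelated to growth) to over 30% (25-33% supported, correlation 0.5), and negative correlations would work against beta-i. These figures assume normal outcomes, ICC 0.05 and 35 YPAOs per arm.

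Aim 2 and its primary outcome are not affected. The point should be fixed, with moderate confidence, because the by-arm reading remains possible.

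**What to change.** Reword Hypothesis 3 in Objectives, and the matching sentence in Sample Size Determination for Aim 3, so that the primary aim 3 contrast is all assessed YPAOs in treatment neighborhoods v all assessed YPAOs in control neighborhoods, by randomized condition. This agrees with the 35 per condition already planned. Report any comparison restricted to supported YPAOs as secondary, call it non-randomized, and adjust it for baseline participation. Limit the causal conclusion about support accordingly.

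The change is one of wording and of one model. All these YPAOs are to be assessed anyway, so no new data are needed.

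The real cost is dilution. If support works only where it is received, the by-arm effect is s times the effect in supported YPAOs. At s = 50%, 0.631 SD becomes 0.316 SD. With SE = sqrt(2 × 1.125/35) = 0.254, one-sided power is Φ(0.316/0.254 − 1.645), about 34%, against 67% for the supported-only contrast if that were free of selection. The plan should say so openly.
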